**Exclusion criteria**
Have undergone a recent primary total knee replacement due to acute traumaAre unable to provide total knee arthroplasty consent

#### Stage 2

We will recruit 150 patients who have been identified as requiring a TKA to take part in the randomized controlled trial being undertaken in this stage of the study. Patients will need to meet the inclusion and exclusion criteria listed in Textbox 2.

Textbox 2.Inclusion and exclusion criteria for stage 2.
**Inclusion criteria**
Have been identified as requiring a primary total knee arthroplasty (unilateral or bilateral) by their treating orthopedic specialistAdult patients (>18 years)Have the capacity to complete a series of self-reported questionnaires (presented in English)
**Exclusion criteria**
Will be undergoing a primary total knee replacement due to acute traumaHave undergone previous knee replacement surgeryHave had knee surgery within the preceding 6 months, have knee surgery scheduled within the next 6 months or are undergoing a revision for existing joint surgeryAre unable to provide informed consent

### Recruitment and Enrollment Procedures

Eligible participants will be contacted by a member of the research team. This will be a follow-up phone call in stage 1, after information has been posted to them; and in stage 2, after they have received the patient information sheet and study information flyer from their surgeon. For stage 2, participants will be recruited from referrals from orthopedic surgeons who undertake total knee replacement procedures at Lake Macquarie Private Hospital, Gateshead, New South Wales, Australia; Lingard Private Hospital, Merewether, New South Wales, Australia; or Maitland Private Hospital, East Maitland, New South Wales. The surgeon and/or their staff will (1) ensure every eligible patient receives a patient information sheet and a flyer, (2) direct patients to contact information for the research team on the patient information sheet/flyer, and (3) share a list of each patient receiving the patient information sheet with the study team. A member of the study team will follow up with each eligible patient via telephone to ensure that they have understood the information they received and to determine if they are interested in participating in the study.

A member of the study team will follow up with each eligible patient via telephone to (1) ensure that they have understood the information they received and (2) determine if they are interested in participating in the study.

Eligible participants can choose not to participate when they receive the patient information sheet and study information flyer. If they do decline to participate, they will not be contacted further. The research team member will ask if the participant has any questions about the study and if they are interested in participating.

If patients opt to have their study questionnaires accessed via the study online platform, they will be provided a copy of the patient information sheet when they access this system via a participant-specific login. Following review of the patient information sheet, they will be asked to acknowledge their consent to participate in the study and provide an electronic consent on the electronic letter of consent. Questionnaire templates will not be accessible to the participants until the consent field on this form has been completed.

If patients opt to have their study questionnaires posted to them, a copy of the patient information sheet and informed consent form will be included in the posted package. Participants will be asked to sign the consent form prior to commencing completion of the questionnaires. The completed consent form and questionnaires will be posted back to the research team.

Participants can decline to participate at any time point during the study, which will not impact their medical care. If patients decide to withdraw from the study, they can specify if their data is to be removed from the study or if they are willing for it to be used as part of the analysis.

### Sample Size

#### Sample Size Estimation and Justification

##### Stage 1

We will initially involve 5 individuals who have undergone a TKA within the last 5 years to take part in video alpha testing encompassing the understandability and actionability of the prototype of the educational videos. Content analysis will be via an inductive approach [60]. If we find that the issues identified in the prototype videos differ substantially between each participant and saturation of the feedback content is not occurring, we will enroll 5 further individuals to undertake the alpha testing, such that feedback from up to 10 individuals will be included in stage 1. The purposive sampling approach being adopted will enable a diverse group of viewpoints to be derived. Taken together with the collaborative approach between the stakeholder groups involved in the design component of this study, we are confident that the number of participants involved in the alpha testing is sufficient to support the development of education materials to be further evaluated in stage 2 of this study.

##### Stage 2

A sample of 150 individuals who have been identified as requiring a TKA by their treating orthopedic specialist (2 subgroups of n=75) will be recruited. This will allow for expected dropouts (approximately 22/150, 15%) and ensure a minimum sample size of 64 for each group, which will enable the study to be adequately powered (see calculations below). A screening log will be kept and will collate reasons why any participants were screened but did not take part in the study.

### Power Calculation: Sample Size Estimate

The number of participants was selected based on previously published findings using the Hospital for Special Surgery Total Knee Replacement Expectations Survey (HSS-TKR) as our primary outcome measure to demonstrate a clinically meaningful change in the overall patient expectation score [35]. Mancuso et al [35] describe a clinically meaningful change in expectations to be associated with a 6-point change in transformed HSS-TKR total scores. To determine a significant difference between 2 groups of patients, such that α=.05, power 80%, and SD 12, will require 64 patients per group. In this study, we will enroll 75 patients per treatment arm to allow for any potential loss of participation at the follow-up time points.

### Randomization Procedures

#### Block Randomization

To ensure a balance in the sample size for each treatment arm during the participant recruitment phase, we will apply block randomization [59]. For a total of 150 recruited participants, we will generate 38 blocks of 4 participants per block with a 1:1 allocation ratio between the intervention and control arms. The randomization list and block allocation details will be generated using software provided by Sealed Envelope Ltd (2022)[] .

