The impact of educational materials generated in stage 1 will be evaluated in a longitudinal, parallel group, 2-armed, block randomization trial with an allocation ratio of 1:1 [59]. Patients undergoing TKA will be enrolled when they have been scheduled for the surgical procedure and will be involved in study assessments for a total of 32 weeks (8 months) from study entry. Referrals of potential study participants will be provided by the participating orthopedic surgeons when their patient has consented to undergo a TKA. The maximum wait time between patient consent and surgery taking place is 6 weeks. Consequently, all presurgery assessments and the study intervention will take place within this 6-week window. Following study consent, baseline assessments will be undertaken at study entry, which is likely to be 5 weeks prior to TKA. The intervention (viewing the educational videos+standard care) or control (standard care alone) will be delivered 4 weeks prior to the scheduled TKA. Standard care will encompass any educational materials provided to the patient by their surgeon and health care provider. For the intervention group, participants will be provided online access to the educational videos. They will have the capacity to view the videos several times if they desire and will record the number of times each one is viewed. Postintervention assessments will be conducted 3 weeks prior to TKA, and postsurgical outcome measures will be undertaken at 6 months following the TKA.

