### Study Setting

The stage 2 randomized trial will be run as a single-center study, centrally managed by the Centre for Rehab Innovations, University of Newcastle, New South Wales. We intend to recruit patients who are scheduled for TKA to take place at private health care facilities within the Greater Hunter Region, New South Wales, Australia and is likely to include, but is not limited to, Lake Macquarie Private Hospital, Gateshead; Maitland Private Hospital, East Maitland; and Lingard Private Hospital, Merewether, New South Wales.

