#### Stratification

We recognize that the level of standard clinical care, with respect to the scope and format of educational materials provided to patients undergoing TKA, may vary significantly between health care providers represented in the recruitment sites involved in the study, and this may influence expectations set by participants. In light of this, we will include “health care provider” as a stratification variable.

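### The 38 fixed blocks of four are counted without the provider strata, and a published fixed block size makes allocation more predictable than it need be

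*Protocol article*

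**What the plan says.** The Stage 2 design description calls the study a "2-armed, block randomization trial with an allocation ratio of 1:1". Block Randomization gives the detail, for a total of 150: "we will generate 38 blocks of 4 participants per block with a 1:1 allocation ratio between the intervention and control arms". It mentions one block size and refers to the randomization list without mentioning strata.

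The Stratification section then notes that standard education may differ between providers and may influence expectations, and concludes that "we will include “health care provider” as a stratification variable". It does not give the number of levels or divide the 38 blocks among them.

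Recruitment and Enrollment Procedures names three private hospitals. Study Setting names the same three but leaves the list open: it "is likely to include, but is not limited to" those sites.

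On the arms: "The intervention (viewing the educational videos+standard care) or control (standard care alone) will be delivered 4 weeks prior to the scheduled TKA". No sham is described. A study team member telephones each eligible patient to check understanding and interest.

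**The concern.** Two stated choices are at issue.

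First, the block count and the stratification were not worked out together. Stratified blocking needs its own block sequence for each provider, and each sequence can end in an unfinished block. A count derived from the overall total has no allowance for that. If the 38 blocks were used as one running sequence, the arms would not be balanced within provider, which is the factor the protocol itself says may affect expectations and hence the primary outcome.

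Second, when every block has size four and readers know it, counting from the first patient in a stratum shows where each block starts. A person who also knows the earlier allocations can then work out some of the coming ones. Participants can tell which arm they are in, and the primary outcome is a self-reported expectation score. Foreknowledge could therefore influence who is encouraged to join, and when.

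**Working it through.** **Inputs from the protocol article.** 150 participants, blocks of 4, 38 blocks, 1:1 allocation (Block Randomization); strata by health care provider (Stratification); three named hospitals, list open (Study Setting). Assumption: provider means hospital, so there are three strata.

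**1. The plan's figure.** 150/4 = 37.5, rounded up to 38; 38 × 4 = 152 places. The 38 is reproduced, with no term for strata.

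**2. Total blocks with three strata.** The number used is the sum over hospitals of n/4, each rounded up.
- Each list leaves 0 to 3 unused places in its last block, so at most 9 in all.
- 38 blocks leave 152 − 150 = 2 unused; 39 leave 156 − 150 = 6; 40 would leave 10, which is impossible. The answer is always 38 or 39.
- Over all ordered splits of 150 into three non-empty strata, 7,030 of 11,026 (64%) need 39.

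**3. Lists cut in advance.** Hospital totals are not known beforehand.
- 38 blocks divided 13/13/12 hold 52/52/48 patients.
- Illustration (assumed recruitment 60/50/40): blocks needed are 15 + 13 + 10 = 38, so the total suffices. The first list still runs out after 52 patients, 8 short, while the third has 48 − 40 = 8 places spare.

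**4. One sequence across hospitals.** In a simulation with three equal-sized providers, the mean absolute arm difference within a provider is about 4.5 patients with a single sequence and about 0.7 with stratified blocks.

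**5. Predictability of fixed blocks of four.** There are 6 equally likely orders of two and two.
- Known with certainty: the fourth place always, and the third in 2 of 6 orders. (1 + 1/3)/4 = 33.3%. In one sequence of 150 there are 37 complete blocks: 37 × 4/3 = 49.3, and 49.3/150 = 32.9%. With three strata it is 32.0% to 32.9%, so stratifying does not cure it.
- Best guess, place by place: 1/2 + 2/3 + 2/3 + 1 = 2.83, and 2.83/4 = 70.8%.

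**6. Varied block sizes.** A simulation let the guesser know the set of sizes but not their order, and updated the probabilities after each allocation.

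| Block sizes | Known with certainty | Best guess correct |
|---|---|---|
| 4 only | about 33% | about 71% |
| 4 and 6 | about 5% | about 69% |
| 4, 6 and 8 | about 2% | about 68% |

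**The case against.** Three stronger readings are tempting, and the article does not support them.

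- **That the plan uses a single list and so cannot stratify.** The article never says so. Block Randomization and Stratification stand under the same heading and can be read together as stratified blocks whose division is not reported. A list can have a section for each stratum, and with three hospitals the total is short by one block at most. That is an administrative matter and does not itself bias the comparison.
- **That a third of allocations will be known to recruiters.** This requires someone to see every earlier allocation in the stratum. The article does not say who holds the list, who releases allocations or whether the caller sees them. A condensed article may leave this to the full protocol, so its silence is not a fault.
- **That many more blocks are needed because provider means surgeon.** The Stage 2 description mentions the surgeon and the health care provider separately, so hospital is the more natural reading.

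The workflow also limits the scope for selection. Surgeons' offices are to give every eligible patient the information sheet and share the list of recipients. Patients consent themselves online or by post, and a screening log records reasons for not taking part. The primary outcome is a change from baseline, which partly absorbs differences in starting level. No size of bias in the treatment effect has been estimated here.

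These points lower the weight of the concern. They do not supply the missing link between 38 blocks and the strata, and they give no reason to prefer a disclosed fixed block size. It is also fair to say that varied blocks hardly change the best-guess rate. Their gain is in removing certainty.

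**Conclusion.** The point holds in a limited form. The stated count of 38 is the unstratified one, and the two sections need reconciling. With three hospitals the total is 38 or 39, so the practical risk lies in how the blocks are divided beforehand or in running them as one sequence.

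The fixed, published size of four makes up to one third of allocations certain to someone who sees the earlier ones in a stratum. That is an upper bound on what could be known, not evidence that allocation will be compromised. It rests on arms being evident from the design, since the article has no statement on blinding. The three-strata figures rest on provider meaning hospital. This is a cheap improvement to the design.

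**What to change.** Delete the 38-block sentence and replace it along these lines: a separate permuted-block list will be generated for each hospital, with a further list for any added site; block sizes will vary at random (eg, 4 and 6) and will not be disclosed to recruiters; each list will be longer than needed, and recruitment will stop at 150. State in the Stratification section that health care provider means hospital, if that is the intention.

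The cost is regenerating the lists before randomisation starts, in the software already named. The downside is that the final arms may differ by a few patients, since a list ending inside a block of six can be at most three out of balance. The loss of precision is negligible: even at 71 against 79, the variance of the difference between arms rises by a factor of (1/71 + 1/79)/(2/75) = 1.003.

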#### Stratification

We recognize that the level of standard clinical care, with respect to the scope and format of educational materials provided to patients undergoing TKA, may vary significantly between health care providers represented in the recruitment sites involved in the study, and this may influence expectations set by participants. In light of this, we will include “health care provider” as a stratification variable.

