##### Content Analysis of Qualitative Data

The interviews will be conducted by either research team member (KR or LS) during a 30-minute, one-to-one session with the research participant. Each interviewer will review the transcript and validate the content, such that it reflects the PEMAT-AV scores for each video. The content concepts will be identified to reflect the acceptability of the prototype videos or potential changes or edits that need to be considered by the research team. To assist with ensuring the dependability of the data, the interviewers will then review the content analysis undertaken by the other interviewer and again undertake their own validation and identification of content concepts for each transcript. Both interviewers will then meet and compare each one’s content analysis and discuss until a consensus is reached. Coding will be undertaken such that classifiers will be applied to the common concepts identified across all transcripts. The interviewers will then determine if content saturation has been achieved or if additional participants will need to be recruited for the alpha testing.

### Stage 2

Descriptive and inferential statistical analyses will be undertaken to describe the characteristics of the participant cohort and to assess the research hypotheses, respectively. Clinical and demographic characteristics will be described using proportions, measures of central tendency (eg, mean and median), and dispersion (eg, SD, IQR). Inferential statistics will be used to test for differences in, or associations between, outcome measures within and between groups of interest. Methods appropriate to both dependent and independent samples (eg, *t* test, ANOVA, and correlation) will be used, including nonparametric methods for data in violation of normality and variance assumptions (eg, Mann-Whitney *U* and Kruskal-Wallis). The threshold for statistical significance will be set at a *P* value of .05.

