To determine the impact of the health education program to change expectations, the primary outcome measure (HSS-TKR) will be measured and compared between the 2 treatment arms. The within-patient changes of the open-ended measures of patient expectations between T_0_ and T2 will also be compared between the 2 treatment arms to further inform the efficacy of the education platform intervention. We will use data from all participants post surgery to determine the association between expectation fulfillment and overall satisfaction. Activity expectation fulfillment satisfaction and overall procedure satisfaction generate ordinal datasets with associations between the 2 measures undertaken using Spearman rank correlation coefficients.

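### Randomisation is stratified by health care provider, but the between-arm analysis as described does not use provider; if provider predicts change in expectations, the test is somewhat conservative and some power is lost

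*Protocol article*

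**What the plan says.** Under Stratification, the protocol article says that the education given as standard care "may vary significantly between health care providers represented in the recruitment sites involved in the study, and this may influence expectations set by participants". For that reason "we will include “health care provider” as a stratification variable". Under Block Randomization, "we will generate 38 blocks of 4 participants per block with a 1:1 allocation ratio between the intervention and control arms".

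Under Data Analysis, Stage 2, the primary analysis is described in one clause: "the primary outcome measure (HSS-TKR) will be measured and compared between the 2 treatment arms". The methods named as examples are the t test, ANOVA and correlation, "including nonparametric methods for data in violation of normality and variance assumptions", with Mann-Whitney U and Kruskal-Wallis as the examples of the latter. Provider does not appear in that section. The only covariates mentioned, under Strengths and Limitations, are clinical, demographic and psychological features, and these relate to satisfaction.

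The sample size is a plain two-group calculation. It is based on "a 6-point change in transformed HSS-TKR total scores", "such that α=.05, power 80%, and SD 12, will require 64 patients per group".

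**The concern.** Stratified blocks balance the arms within each provider, so differences between providers largely cancel out of the arm difference. The true sampling error of the estimate therefore no longer contains the between-provider variance. A two-sample test that ignores provider still counts that variance in its estimated error. The standard error is then too large, the P value too high on average, and the precision bought by stratifying is not used.

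The protocol's own reason for stratifying is that provider education may affect expectations, and expectations are what the primary outcome measures. At stake is some power and a correctly sized test. The validity of the treatment estimate is not in question.

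**Working it through.** **Inputs from the protocol article.** Difference 6 points, SD 12, alpha .05, 80% power and 64 per group (Power Calculation); blocks of 4 at 1:1 (Block Randomization); three named hospitals (Recruitment and Enrollment Procedures, including "Lingard Private Hospital, Merewether, New South Wales, Australia; or Maitland Private Hospital, East Maitland, New South Wales").

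**Assumed input.** The share r of the outcome variance that is due to provider. The documents give no figure, so the range 0 to 0.20 is shown.

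**Step 1: reproduce the plan's figure.** The normal approximation gives n = 2 × (1.96 + 0.842)² × (12/6)² = 62.8, so 63 per group. The two-sample t test gives 63.77, so 64. The stated 64 is reproduced with a two-sided alpha.

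**Step 2: formulas.** Hold the total SD at 12. The standardised difference is 6/12 = 0.5. With 64 per arm, its expected z value is 0.5 × √32 = 2.828. With provider in the model, the residual SD is 12 × √(1 − r). Then:

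- standard error ratio, unadjusted to adjusted = 1/√(1 − r)
- true two-sided type I error of the unadjusted test = 2 × [1 − Φ(1.96/√(1 − r))]
- power, unadjusted = Φ[(2.828 − 1.96)/√(1 − r)]
- power, adjusted = Φ[2.828/√(1 − r) − 1.96]

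These formulas assume good balance within providers.

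**Step 3: results.**

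| Assumed r | SE too large by | Type I error, unadjusted | Power, unadjusted | Power, adjusted | Patients per arm for 80% power, adjusted (normal approximation) |
|---|---|---|---|---|---|
| 0 | 0% | 5.0% | 80.7% | 80.7% | 63 |
| 0.05 | 2.6% | 4.4% | 81.4% | 82.7% | 60 |
| 0.10 | 5.4% | 3.9% | 82.0% | 84.6% | 57 |
| 0.20 | 11.8% | 2.8% | 83.4% | 88.5% | 51 |

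For example, at r = 0.20, √(1 − r) = 0.894. The ratio is 1/0.894 = 1.118; unadjusted power is Φ(0.868/0.894) = Φ(0.971) = 83.4%; adjusted power is Φ(3.162 − 1.96) = Φ(1.202) = 88.5%.

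**Step 4: check by simulation.** The set-up was three providers equally likely, permuted blocks of 4 within provider, 128 patients in all, 8,000 runs per setting, and a linear model without and with provider.

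| Assumed r | Type I error, without v with provider | Power, without v with provider | Mean 95% interval width under the null, without v with provider |
|---|---|---|---|
| 0 | 4.4% v 4.4% | 79.8% v 79.8% | 8.38 v 8.38 |
| 0.05 | 4.3% v 4.9% | 80.6% v 82.0% | 8.39 v 8.18 |
| 0.10 | 3.8% v 4.7% | 80.6% v 83.5% | 8.38 v 7.95 |
| 0.20 | 2.8% v 4.8% | 82.7% v 87.8% | 8.38 v 7.49 |

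The Monte Carlo standard error of a 5% rate is √(0.05 × 0.95/8,000) = 0.24 percentage points. The 4.4% in both columns at r = 0 should therefore be read as noise common to the two tests, and the formula values are preferable for the level of the type I error. The simulation confirms the direction and the size of the difference. At r = 0.20 it puts adjusted power at 87.8% against 88.5% by formula, hence about 88%.

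**The case against.** **An unseen analysis plan may contain the provider term.** This is the strongest objection. An article condenses, and the model's covariates are often left to the analysis plan. The methods are listed only as examples, ANOVA can carry a provider factor, and an adjusted model also compares two arms. A reader might infer that the protocol commits to an unadjusted test or excludes provider; the text does neither. What remains is that the article names its test families and gives its reason for stratifying without connecting the two. The rank tests it names cannot carry a stratum, so that fallback, used as named, ignores the stratification.

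**The harm is conditional.** A reader might infer that the intervals will be too wide. The documents do not support that as a fact. The article says only that care may differ and may influence expectations, gives no provider share of variance, and states a P value threshold with no mention of confidence intervals. The primary outcome is also a within-patient change, which removes stable provider differences. Only provider effects on change between baseline (about 5 weeks before surgery) and reassessment (3 weeks before) matter. This stands, but it does not dispose of the point: standard care is delivered to both arms between those two assessments, so provider-specific education can affect the change. Fulfilment and satisfaction are measured only at 6 months and have no baseline value to subtract.

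**The consequence is mild.** This also stands. A reader might infer bias, excess false positives or an underpowered trial. None follows: the estimate is unbiased, the error is in the conservative direction, and unadjusted power by formula is at least 80% in every scenario.

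**The set-up may be less tidy than assumed.** The article does not define whether provider means hospital or surgeon, and Study Setting leaves the list of sites open. Replacements take the arm of the withdrawn participant with no mention of provider, so balance may be looser than in the formulas. These points affect the exact figures and the degrees of freedom spent, but not the direction.

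**Conclusion.** The point holds as a modest, conditional loss of efficiency. The stratification factor chosen because it may matter for expectations is absent from the described between-arm analysis. The cost of leaving it out depends on how much of the variance in HSS-TKR change is due to provider. It is nothing at a share of zero, about 1 percentage point of power at 5%, and about 5 points at 20%, where the test runs at about 2.8% in place of 5%.

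These figures rest on an assumed range for the share, a total SD of 12, 64 analysed per arm and good balance within provider. The upper end is illustrative and is not a forecast. No corresponding size has been worked out for the secondary outcomes. The change is worth making because it is nearly free. The design's stated target does not fail without it.

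**What to change.** In Data Analysis, Stage 2, state that the primary between-arm model for HSS-TKR includes health care provider, coded exactly as in the randomisation, as a fixed effect. Name a provider-stratified rank test (van Elteren) in place of the plain Mann-Whitney U as the nonparametric fallback. Apply the same to the between-arm secondary comparisons (fulfilment, satisfaction, health literacy), using the stratified rank test or an ordinal regression with provider where the outcome is ordinal. Define in the same place whether provider means hospital or surgeon, so that the number of strata is known. If a separate analysis plan already contains the term, one sentence in the protocol is enough.

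The cost is wording plus one degree of freedom per additional stratum, which is two if the strata are the three named hospitals. The variable is already needed for randomisation, and the sample size need not change. Fixing the model in advance also removes any later choice between adjusted and unadjusted results.
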